## Abstract

**Background:**

There is a need to develop sustainable and clinically effective weight management interventions that are suitable for delivery in community settings where the vast majority of overweight and obese adolescents should be treated. This study aims to evaluate the effect of additional therapeutic contact as an adjunct to the Loozit^® ^group program – a community-based, lifestyle intervention for overweight and lower grade obesity in adolescents. The additional therapeutic contact is provided via telephone coaching and either mobile phone Short Message Service or electronic mail, or both.

**Methods and design:**

The study design is a two-arm randomised controlled trial that aims to recruit 168 overweight and obese 13–16 year olds (Body Mass Index z-score 1.0 to 2.5) in Sydney, Australia. Adolescents with secondary causes of obesity or significant medical illness are excluded. Participants are recruited via schools, media coverage, health professionals and several community organisations. Study arm one receives the Loozit^® ^group weight management program (G). Study arm two receives the same Loozit^® ^group weight management program plus additional therapeutic contact (G+ATC). The 'G' intervention consists of two phases. Phase 1 involves seven weekly group sessions held separately for adolescents and their parents. This is followed by phase 2 that involves a further seven group sessions held regularly, for adolescents only, until two years follow-up. Additional therapeutic contact is provided to adolescents in the 'G+ATC' study arm approximately once per fortnight during phase 2 only. Outcome measurements are assessed at 2, 12 and 24 months post-baseline and include: BMI z-score, waist z-score, metabolic profile indicators, physical activity, sedentary behaviour, eating patterns, and psychosocial well-being.

**Discussion:**

The Loozit^® ^study is the first randomised controlled trial of a community-based adolescent weight management intervention to incorporate additional therapeutic contact via a combination of telephone coaching, mobile phone Short Message Service, and electronic mail. If shown to be successful, the Loozit^® ^group weight management program with additional therapeutic contact has the potential to be readily translatable to a range of health care settings.

**Trial registration:**

The protocol for this study is registered with the Australian Clinical Trials Registry (ACTRNO12606000175572).

## Background

### Study context

This study was designed to address the apparent gap in service provision of sustainable community-based weight management programs for overweight and obese adolescents. The Loozit^® ^group weight management program is a modest intensity, evidence-based, healthy lifestyle intervention delivered over a two year period. Instead of providing a higher level of direct contact with participants, this study provides adolescents with additional therapeutic contact via telephone coaching and mobile phone Short Message Service (SMS) and/or electronic mail (e-mail). These modes of communication offer the capacity to provide regular and engaging therapeutic contact with a greater number of adolescents than could be sustained in traditional programs involving only direct contact with participants. Here we give an overview of the literature that has guided the development of this study.

### Obesity in adolescence

The prevalence of adolescent overweight is increasing in almost all developed countries and several developing countries [1] making it one of the most common chronic disorders in this age group [2]. Adolescence is a period of major physical and cognitive change and increasing independence when alterations to eating behaviour, physical activity and other aspects of lifestyle may be maintained into adulthood [3,4]. Adolescence has been termed a "critical period" for the development of adult obesity [5] and adolescents with established overweight or obesity have a moderate to substantial risk of remaining so in adulthood [6]. Overweight and obese adolescents also suffer a range of immediate and long-term medical and psychosocial complications [7,8]. Thus, interventions at this developmental stage may be crucial for present well-being, long-term weight management, and the avoidance of entrenched co-morbidities.

### Obesity management: a continuum of chronic disease care

Obesity is a chronic and often a life-long disease. Therefore its treatment may best be considered within the broad framework of the Chronic Care Model [9] and associated service delivery models, such as the Kaiser model [10]. The Kaiser model proposes that three levels of chronic disease care need to be offered within a health care system. Level 1 care, suitable for the vast majority of affected individuals, emphasises the patient's (or the patient's familiy's) central role in managing their health, in conjunction with primary care doctors and the effective use of community and other health system resources. Level 2 involves care of high risk patients by multidisciplinary disease management protocols, and Level 3 is active case management of highly complex patients [10]. To date, there are no published reports of such a country or state wide approach to obesity management.

### Treatment of adolescent obesity

The conventional components of weight management in adolescents and children include dietary modification, increased physical activity, decreased sedentary activity, behaviour modification and family involvement [11]. There is only limited evidence to guide effective weight management interventions in the adolescent age group that would be sustainable in most health care settings. The 2009 Cochrane review of interventions for treating obesity in children included 27 randomised controlled trials (RCTs) involving adolescents (i.e. mean age > 12 years). The primary type of intervention was behavioural lifestyle modification in 12 studies, pharmacotherapy in 10 studies, physical activity in three studies, and diet in two studies. Meta-analyses indicated a reduction in overweight at 6 and 12 months follow-up in lifestyle interventions with or without the addition of the drugs orlistat or sibutramine [11]. The majority of the interventions included in the 2009 Cochrane review were of relatively high intensity and offered in settings that would be classified as Level 2 or 3 care as per the Kaiser model. There remains a need for more RCTs of adolescent obesity treatments that would be sustainable in Level 1 (i.e. community and primary care) settings.

### Extended therapeutic contact for weight loss maintenance

Sustained weight loss in the long-term (i.e. 2–4 years) following non-surgical treatment of overweight and obesity is modest at best in adults who complete interventions [12] but this outcome may be different in children and adolescents, particularly in those with height growth potential. Few high quality studies have reported long-term outcomes of child and adolescent obesity treatment [11] but in those that have, a high proportion of participants maintained a reduction in overweight up to 10 years after commencing treatment [13,14]. Persisting with positive lifestyle changes appears to be a universal and key factor in successful weight loss maintenance [15,16]. In overweight and obese children and adolescents who have completed an initial course of weight management treatment there appears to be a beneficial effect of extended therapeutic contact (varying from 4–12 months) in slowing weight regain [17,18]. Yet there remains little evidence as to the optimal format and duration that extended therapeutic contact should take for the treatment of adolescent obesity.

### Strategies for extended therapeutic contact for adolescents with chronic disease

The use of telephones [19], mobile phone SMS [20] and interactive technologies such as e-mail or the Internet [21], can be an effective means of providing therapeutic interventions for health behaviour change. These modes of communication are commonly accessible and frequently used by adolescents [22,23] and therefore have the capacity to better engage adolescents in health interventions. Treatments for child and adolescent overweight and obesity have incorporated telephone interventions for over 20 years [11] but the use of e-mail/internet [24-26]and mobile phone SMS [27] in the same role has only emerged in recent years and requires further research in high quality studies [20,21]. Each of these communication modes differs with regards to cost, time required to communicate with multiple recipients, ability to communicate detailed information, and immediacy of access to recipients [28]. Therefore a combination of these communication methods may be an effective means of providing extended therapeutic contact in a weight management program for overweight and obese adolescents.

### Pilot work for a community-based obesity treatment intervention for adolescents

Community health centres in countries such as Australia [29] and the United States [30] are generally located close to residential areas and are therefore a potentially viable setting for adolescent overweight and obesity treatment suitable to Level 1 care as per the Kaiser model. In 2004/2005 we conducted and evaluated a 5-month pilot study of a community based lifestyle intervention for weight management in overweight and obese 13–16 year olds [31]. The pilot intervention consisted of seven group sessions for adolescents and focused upon achievable goals for dietary intake, physical activity, sedentary behaviour, and strategies for increasing self-esteem. The program was named Loozit^® ^by the participating adolescents. Results from that pilot study confirmed the intervention was feasible to run and acceptable to the adolescents. Although the pilot study was statistically underpowered and only of modest intensity, there was a statistically significant improvement in waist circumference, HDL-cholesterol and several of the Harter Self Perception Profile domains (physical appearance and romantic appeal) [31]. Feedback from adolescents and their parents was collected through focus groups and used, together with the group leader's evaluations, to refine the original program's content, structure, and recruitment strategies to form the current Loozit^® ^program. Compared with the original pilot study intervention, the current Loozit^® ^program now includes group sessions for parents/carers and a maintenance phase for adolescents involving 'booster' group sessions and additional therapeutic contact (i.e. via telephone coaching, and mobile phone SMS and/or e-mail) which will be referred to hereafter as ATC. With these modifications the current program is still suitable for Level 1 treatment and meets the recommendations of the Australian *National Health & Medical Research Council Clinical Practice Guidelines *[32].

### Study rationale

To our knowledge, the current study is the first RCT of a sustainable, community-based, weight management program for overweight and obese adolescents that will evaluate the effect of ATC, in the form of a combination of communication strategies (i.e. via telephone coaching, and mobile phone SMS and/or e-mail) as an adjunct to a group program over a two year period.

## Aims and hypotheses

The primary aim of the study is to determine the effect of ATC to usual treatment on body mass index (BMI) z-score and waist circumference z-score in overweight and obese adolescents aged 13–16 years (at baseline) who participate in a community-based weight management program (the Loozit^® ^group program). Adolescents enrolled in the study are randomised to receive one of the following two interventions: the Loozit^® ^group program (G); or the Loozit^® ^group program + additional therapeutic contact (G + ATC). ATC includes a combination of telephone coaching, and mobile phone SMS and/or e-mail messages. It is hypothesised that:

1. compared to baseline, both the G and the G+ATC interventions will result in a clinically relevant and a statistically significant:

a) reduction in BMI z-score and in waist circumference z-score (primary outcomes) at 2, 12 and 24 months post-baseline;

b) improvement in other important outcome measures in weight management including metabolic profile indicators, eating patterns, physical activity, sedentary behaviour, and psychosocial well-being (secondary outcomes) at 2, 12 and 24 months post-baseline; but that

2. the G+ATC intervention, relative to the G intervention, will produce a clinically relevant and a statistically significant greater reduction in the primary and secondary outcomes outlined above at 12 and 24 months post-baseline, as well as better retention in the program.

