## Methods and design

### Study design

The overall study design is summarised in Figure 1. This study is registered with the Australian Clinical Trials Registry (ACTRNO12606000175572) and has been approved by the Human Research Ethics Committees of: The Children's Hospital at Westmead, Sydney West Area Health Service, and The University of Sydney.

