#### Eligibility criteria

The inclusion and exclusion criteria for assessing adolescent eligibility to participate in the study (Table 1) are used during a telephone screen that is conducted with whoever enquires about the study (e.g. parents/carers, adolescents, health professionals or school counselors). Each enquiry about study participation is issued with a unique identification number that is used to distinguish individuals throughout the study. Adolescents who meet the study criteria are invited to an appointment with a research assistant, along with their parents/carers, in order to confirm eligibility based on objectively measured weight status. Informed consent or assent, depending on age, is obtained from adolescents who meet the study eligibility criteria and wish to participate. Consent is also obtained from one of the adolescent's parents/guardians. Although many adolescents are found to be ineligible during the telephone screen, it is uncommon for adolescents to be found ineligible at the appointment. Adolescents who are ineligible to participate, and their parents/carers, are encouraged to follow up with their general practitioner.

**Table 1 T1:** Inclusion and exclusion criteria for adolescent participation in the Loozit^® ^study

**Inclusion criteria**	**Exclusion criteria**
▪ Age 13.0–16.9 years	▪ Severely obese (i.e. BMI z-score^a ^>2.5) or if there is a secondary cause for overweight/obesity
▪ Overweight to moderately obese (i.e. BMI z-score^a ^range 1.0–2.5)	▪ Intellectual disability, significant medical illness, psychiatric disturbance
▪ Home access to a landline telephone	▪ Taking medications that affect weight status
▪ Home access to the internet to receive e-mails or access to a mobile phone to receive SMS messages	▪ Inability to take part in physical activity sessions
▪ Ability to attend the group program for 7 weeks in the first instance on the specified days^b^	▪ Poor level of spoken English (adolescent or parent/carer)
▪ At least one of the adolescent's parents/carers must be willing to also participate in the initial 7 parent group sessions	

^a ^calculated using Centers for Disease Control growth reference [41]

^b ^The 'G' and 'G +ATC' group programs are run on separate weeknights and therefore potential participants need to be available to attend on either evening, pending randomisation, even though they would only attend once per week

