#### 1) Loozit^® ^group program (G)

##### i) Background

The key aspects covered in the Loozit^® ^group program are in keeping with Australian clinical guidelines for the management of overweight and obesity [32] and include healthy food choices and eating patterns, increasing physical activity and reducing sedentary behaviour, strategies for managing behaviour change with a focus on goal setting, dealing with stress and building self-esteem. The program is based upon a cognitive behavioural approach using behavioural principles to change dietary intake and activity levels, and social cognitive approaches to modify self-efficacy, motivation, perseverance and self-regulation [37].

Participants in both arms of this study receive the Loozit^® ^group program (G) which is provided separately to adolescents and their parents/carers. Separate skills training sessions for parents have been shown to help weight loss in adolescents [38], and this approach was requested by both parents and adolescents in focus groups held as part of the pilot study that preceded the current study [31]. The Loozit^® ^group program is run over a 24 month period and is divided into two distinct phases. Phase 1 consists of seven group sessions for adolescents and their parents/carers that take place weekly for seven consecutive weeks during a school term. This is followed by phase 2 which involves a further seven group sessions for adolescents, called 'booster' group sessions, held once every school term (approximately once every three months to 24 months post-baseline).

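### Hypothesis 1 credits within-arm change from baseline to the interventions, but both arms receive the group program, so the design can identify only the effect of adding ATC

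*Protocol article*

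**What the plan says.** Under Aims and hypotheses, the protocol article gives a between-arm aim: "The primary aim of the study is to determine the effect of ATC to usual treatment on body mass index (BMI) z-score". Two hypotheses follow. The first is within-arm: "compared to baseline, both the G and the G+ATC interventions will result in a clinically relevant and a statistically significant" change, which item (a) specifies as "reduction in BMI z-score and in waist circumference z-score (primary outcomes) at 2, 12 and 24 months post-baseline". The second compares G+ATC with G at 12 and 24 months.

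On the design, the abstract states: "The study design is a two-arm randomised controlled trial". The Background to the Loozit group program says: "Participants in both arms of this study receive the" group program. No untreated, waiting-list or other arm without the program is described. ATC is given in phase 2 only, and the 2-month assessment falls at the end of phase 1.

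On entry, the abstract describes "overweight and obese 13–16 year olds (Body Mass Index z-score 1.0 to 2.5", and Eligibility criteria adds an appointment "in order to confirm eligibility based on objectively measured weight status".

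The Sample size section, the contrasts under Planned data analysis and the Discussion all address the comparison between arms. Nowhere is the within-arm change called uncontrolled or descriptive.

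**The concern.** Hypothesis 1 is worded causally, refers to the primary outcomes and requires statistical significance. It covers 2 outcomes × 3 times × 2 arms = 12 within-arm statements. None of them can be attributed to the program, because there is no concurrent group without it.

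Participants are admitted because their measured BMI z-score is high, and the same quantity is then a primary outcome, so some fall on re-measurement is expected with no treatment at all. Motivated volunteers, secular change and selective loss also act on the within-arm change. Not all of these push it downwards. The Background says that adolescent overweight is becoming more common, which would work against a fall. The problem therefore runs both ways: a fall does not show that the program works, and the absence of one does not show that it fails.

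What is at stake is the conclusion the trial may draw about the group program itself, not its conclusion about ATC.

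**Working it through.** **1. The plan's own figure.** Inputs from Sample size: difference 0.4, SD of change 0.8, two-sided 0.05, two-group t-test. The normal approximation gives n = 2 × (1.96 + 0.842)² × 0.8² / 0.4² = 62.8, so 63 per arm. The noncentral t gives power 0.801 at 64 per arm. The stated 64 is reproduced, and it serves the between-arm comparison only.

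**2. What a within-arm test would call significant.** With n = 64 and SD 0.8, SE = 0.8 / √64 = 0.10. The smallest significant mean fall is 1.998 × 0.10 = 0.20, half of the 0.4 units.

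**3. Expected fall with no program effect.** The documents give neither the correlation between baseline and follow-up (ρ) nor the source population, so both are assumptions here. Take source z-scores as N(0,1), with entrants truncated to 1.0–2.5:

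- Mean at entry = (0.24197 − 0.01753) / (0.99379 − 0.84134) = 1.472.
- Expected fall = (1 − ρ) × 1.472.
- In this model, SD of change = √[(1 − ρ)² × 0.3636² + 1 − ρ²], where 0.3636 is the SD among entrants.

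Chance of a significant fall in one arm, for BMI z-score at one time point, n = 64, two-sided 0.05 (nominal chance of a false fall 2.5%):

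| ρ | Expected fall | Chance at SD 0.8 | SD implied by ρ | Chance at implied SD |
|---|---|---|---|---|
| 0.98 | 0.029 | 0.047 | 0.199 | 0.213 |
| 0.95 | 0.074 | 0.108 | 0.313 | 0.458 |
| 0.90 | 0.147 | 0.305 | 0.437 | 0.755 |

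Counting significant changes in either direction, the normal approximation at SD 0.8 gives 0.114 at ρ = 0.95 and 0.312 at ρ = 0.90, against a nominal 0.05. If the source mean is 0.5 instead of 0, the expected falls are 0.05 and 0.10, and the chances at SD 0.8 are about 8% and 18%.

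**4. Clinical relevance as well.** If 0.4 is the threshold and SE = 0.10, the chance that regression alone yields an observed mean fall of at least 0.4 in one arm is:

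- ρ = 0.95: P(Z > (0.4 − 0.074) / 0.10) = P(Z > 3.26), about 0.06%.
- ρ = 0.90: P(Z > (0.4 − 0.147) / 0.10) = P(Z > 2.53), about 0.6%.

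**5. Both arms significant.** Treating the arms as independent: 0.11² ≈ 1% to 0.31² ≈ 10%.

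**The case against.** The strongest reply is that the plan already rests on the right comparison. The primary aim, sample size, time-by-group interaction and planned contrasts are all between arms. No within-arm test is named or powered, and the Discussion says that the trial will determine whether ATC improves outcomes. That is correct, and it confines the point to hypothesis 1. It does not remove the point, because hypothesis 1 still stands as a causal, significance-based statement on the primary outcomes.

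A reader might infer that an ineffective program would readily satisfy hypothesis 1 in both arms. The documents do not support that. The hypothesis requires clinical relevance as well as significance. If that means the 0.4 units of the Sample size section, steps 4 and 5 show how rarely falls of 0.07 to 0.15 would get there. Some uncertainty remains, because hypothesis 1 itself carries no threshold and the 0.4 is given for a one-year period.

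The illustration has other limits. ρ and the source population are assumed. SD 0.8 does not fit ρ of 0.90 to 0.95 when the population SD is 1, which is why the implied SDs are tabulated. The outcomes are age- and sex-specific z-scores, so average growth is already removed. Waist z-score is not an entry criterion and would regress only through its correlation with BMI. The 30% dropout is a planning allowance, and no direction of bias follows from it. All of this bears on the size of the effect. The identification argument depends on none of it.

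**Conclusion.** The point holds. Without an arm that goes without the program, a significant within-arm fall cannot be attributed to G or to G+ATC as a whole. At 2 months the arms have had the same treatment, so there is no randomised contrast to fall back on.

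The size is uncertain. Under the stated assumptions regression alone gives a fall of 0.07 to 0.15, with about an 11% to 31% chance of significance in one arm at one time. At ρ = 0.98 it is a negligible 0.03. The implied SDs raise the chance of significance but leave the expected falls well short of 0.4.

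Two stronger inferences should be resisted. First, solving the same model for SD 0.8 gives ρ of about 0.62 and a no-effect fall of 0.40 to 0.57 (source mean 0.5 to 0), so a reader might conclude that regression alone would reach the clinical threshold. The documents do not establish this: 0.8 is a planning assumption, and neither the correlation nor the population SD is given. Second, a reader might conclude that the trial's main comparison is compromised. It is not: regression to the mean is expected equally in both randomised arms, and the sample size and planned contrasts concern their difference.

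**What to change.** Restate hypothesis 1 as a descriptive estimate of change from baseline in each arm, with confidence intervals. It should not be a confirmatory test, and the change should not be attributed to the program. Keep confirmatory and causal wording for hypothesis 2, G+ATC versus G at 12 and 24 months, in line with the primary aim, sample size and planned contrasts. Wherever within-arm changes are reported, say that they are uncontrolled and that entry was selected on BMI z-score.

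The cost is wording only: no change to recruitment, data collection or the randomised analysis. The downside is giving up a claim about the group program that this design cannot support.
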